### Patient and Public Involvement Statement

There was no involvement in the design and development of this trial by patients or the public. The public will be involved in the dissemination of the research. An end of study report will be developed to communicate study results to all participants, and a study newsletter will be sent to participants via email.

### Statistical Analysis Plan

Normality and homoscedasticity data assumptions will be checked using Kolmogorov-Smirnov (K-S) and Levene tests. Significant differences on categorical variables (eg, sex, educational level, occupation, etc) will be assessed using a chi-square test. Attrition and dropout rates will be calculated by reporting percentages and patterns of missing data. The Little missing completely at random (MCAR) test will be used to assess the assumption that data are MCAR [55]. Means and SDs will be reported for all the measures at each assessment point. A preliminary efficacy analysis will be performed using means of comparison for related samples based on intention-to-treat and per-protocol analyses. Mixed model analyses for primary and secondary outcome measures will be implemented using the linear mixed-effects models (MIXED) procedure with 1 random intercept per subject. *Time* will be treated as a within-group factor, and significant effects will be followed up with pairwise comparisons (adjusted by a Bonferroni correction). Sensitivity analyses will be performed to assess the robustness of the findings in terms of different methods for handling missing data (ie, mixed models with and without imputation, maximum-likelihood estimation, and maximum-likelihood multiple imputation) [56]. Within-group effect sizes (pre vs post and pre vs 3-month follow-up) will be reported using Cohen *d* and its 95% CI. For the analyses of associations between the intervention outcomes, predictors of change, and mechanisms of actions, several statistical tests will be performed such as Pearson correlation, multiple regressions, and mediation analysis using the bootstrapping approach [57]. A cost-effectiveness and cost-utility analysis will be conducted using the GHQ-12 based on literature proposals [58,59]. The mapping technique proposed by Lindkvist and Feldman [59] will be used to predict health state utility values using a crosswalk transformation algorithm from the GHQ-12 to the health utility measure (EuroQoL–5 dimension [EQ-5D]). Spanish tariffs of EQ-5D will be used as the reference population [58,60]. Additionally, participants’ qualitative responses regarding adverse or unwanted effects and facilitators and barriers to the intervention received will be explored using a qualitative content analysis and coding and the categorizing data approach by counting the frequency of words with NVivo software (QSR International). Statistical analyses of quantitative data will be performed using SPSS version 23 for Windows (IBM Corp). The statistical analysis plan (SAP) will be revised by all the study team members before the database is locked for use in the final statistical analysis. Any discrepancies or changes made between the analysis plan in this protocol and final SAP will be explained and reported.

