### Aims and Hypotheses

The main aim of this study is (1) to investigate the feasibility of the Internet Attachment–Based Compassion Therapy (iABCT), a web-based version of ABCT, in the general population. Additional objectives are (2) to analyze the preliminary effects of iABCT on happiness, compassion, self-compassion, dispositional mindfulness, general health, purpose in life, nonattachment, attachment styles, self-criticism, and positive and negative affects at postintervention and 3-month follow-up; (3) to explore cost-effectiveness by means of changes in overall health status levels; (4) to investigate the mechanisms of change, predictors, and associations between outcomes; and (5) to assess adverse or unwanted effects and facilitators and barriers to the intervention received.

The principal hypothesis is that iABCT will be feasible and well accepted by participants in terms of attrition, expectations, satisfaction, usability, and opinion. Second, iABCT will show efficacy in promoting significant changes with moderate-to-large within-group effect sizes in self-reported measures of happiness, compassion, self-compassion, dispositional mindfulness, self-criticizing, nonattachment, purpose in life, attachment, and overall health status. We also hypothesize that gains will be maintained at 3-month follow-ups. Third, changes in overall health levels will demonstrate the cost-effectiveness of iABCT. Fourth, significant associations will be found between changes in compassion, self-compassion, dispositional mindfulness, general health, purpose in life, nonattachment, attachment styles, self-criticism, positive and negative affects, and happiness. Specifically, improvements in happiness scores and overall health status will be predicted by self-reported self-compassion. Increments in secure attachment style would mediate the relationship between self-compassion and happiness. Finally, low rates of adverse or unwanted effects are expected.

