## Methods

### Study Design

This feasibility study and open trial features a single-arm, uncontrolled, within-group design with 3 measurement points at baseline (preintervention), immediately after the intervention (postbaseline), and 3-month follow-up with an embedded qualitative and quantitative assessment. Participants will be allocated to iABCT. The study was registered under Clinicaltrials.gov (NCT03918746) and will be conducted following the extension of the Consolidated Standards of Reporting Trials (CONSORT) statement for pilot and feasibility studies [29], the Consolidated Standards of Reporting Trials of Electronic and Mobile HEalth Applications and onLine TeleHealth guidelines [30], and the Standard Protocol Items: Recommendations for Interventional Trials (SPIRIT) guidelines (Multimedia Appendix 1) [31]. The SPIRIT checklist was used as a guide for reporting this study protocol (version 1; March 6, 2019).

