### Sample Size

A minimum of 35 participants is considered sufficient to cover the aims of this feasibility study and to provide precise and efficient estimations of parameters (ie, means, standard deviations, effect size, and confidence intervals) for the powering of a larger RCT. Sample estimation is based on the recommended range in the literature (eg, 24 and 50) [33-35] and in line with existing feasibility studies in this field [25,26].

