**Figure 1 figure1:**
[figure not shown]
A screenshot of the “Psicología y Tecnología” (Psychology and Technology) Web platform.

Table 1 presents the contents of each module. In comparison with the original ABCT, the adapted web-based version includes module 0, “Introduction to attachment-based compassion therapy,” to introduce to the participant the basics of the attachment-based compassion model and the program contents. Module 0 also includes tips about the use of formal and informal compassion (when/where/how much/how meditate) and on the importance of progressiveness in compassion training and of home practice between modules. Specific content has been added about “managing guilt” (formal meditation in module 4), “embarrassment” (theoretical component and formal practice in module 5), and “envy” (theoretical component and formal practice into module 7). Moreover, the term, “the figure of affect,” has been replaced by “basic affection” to make it easier to understand and so that participants will not confuse this with “the figure of secure attachment.” Other practices that have been eliminated are “showing forgiveness for the hurt caused by loved ones” (for people with grief experiences) and the “the illusion of labels” because they were not considered relevant for this protocol. Finally, module 8 on equanimity (“Beyond compassion: equanimity”) [6] has not been included in the web-based version because it was considered a different and advanced aspect of compassion.

The length of the interventions will depend on the pace of each participant, who will be advised to complete 1 module per week, taking the days between sessions to complete homework assignments. Each module has been optimized to allow it to be completed in approximately 1 hour. It is estimated that the web-based intervention can be completed in 8 weeks. However, each participant will be free to advance at his/her own pace with a maximum period of 10 weeks. Formal telephone support will not be systematically provided, but participants will be able to make contact for technical assistance (eg, web accessibility problems or forgotten passwords) if necessary.

**Table 1 table1:** Structure and contents of Internet Attachment–Based Compassion Therapy.

Module	Theoretical component	Formal practice	Informal practice

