### Outcome Measures

Participants will be assessed at baseline (preintervention), postintervention, and 3-month follow-up after they complete the intervention. Assessments will be conducted online via the website [36], where the iABCT will be hosted, and via a telephone interview at pre- and postintervention, except for the 3-month follow-up that will be conducted only via the website. Both participants and researchers will receive email reminders of each assessment time. The study variables and assessment times are summarized in Table 2.

**Table 2 table2:** Study measures, time of assessment, and source of measurement.

Measures	Aim	Assessment point	Assessment source
Admission interview	Screen eligibility criteria (inclusion/exclusion)	Pre^a^	Phone interview
Sociodemographic data	Sex, age, educational level, occupation, and civil status	Pre	Phone interview
M.I.N.I. 7.0.2.^b^	Psychological diagnosis (exclusion criterion)	Pre	Phone interview
Meditation data	Source of learning, frequency, duration of each session (in minutes), lifetime practice (in years), and context of practice	Pre	Phone interview
PHI^c^	Well-being	Pre, post^d^, and FW^e^	Web
SCS-26^f^	Self-compassion	Pre, post, and FW	Web
Compassion scale	Compassion	Pre, post, and FW	Web
FSCRS-SF^g^	Two forms of self-criticism: inadequate self and hated self and the ability to self-reassure	Pre, post, and FW	Web
FFMQ-15^h^	Dispositional mindfulness and mindfulness facets	Pre, post, and FW	Web
RQ^i^	Attachment styles	Pre, post, and FW	Web
GHQ-12^j^	Mental health recent symptoms, feelings, or behaviors	Pre, post, and FW	Web
NAS-7^k^	Nonattachment	Pre, post, and FW	Web
I-PANAS-10-SF^l^	Positive and negative affects	Pre, between modules, post, and FW	Web
PIL-10^m^	General sense of meaning and purpose in life	Pre, post, and FW	Web
Compassion Practice Quality Questionnaire	Difficulties related to the practice of compassion meditation	Between modules, post, and FW	Web
Expectations and Satisfaction Questionnaires	Participants’ expectations before the intervention and their satisfaction after it	Pre and post	Web
UAQ^n^	Usability and acceptability of the internet-based intervention	Post	Web
Qualitative opinion interview	Opinions on the internet intervention, the modules, and unwanted or unexpected effects	Post	Phone call
Attrition rate	Percentage of participants that drop out of the intervention after accessing it for the first time	Post	Web

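### The random-intercept-only mixed model assumes one common correlation across three unequally spaced waves; if correlation falls with time, the baseline-to-follow-up test rejects too often

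*Protocol article*

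**What the plan says.** The Statistical Analysis Plan section of the protocol article names the "linear mixed-effects models (MIXED) procedure with 1 random intercept per subject" for primary and secondary outcomes. Time is a within-group factor, and significant effects lead to pairwise comparisons with a Bonferroni correction. No residual covariance structure is named. The sensitivity analyses listed there compare ways of handling missing data. The same section also plans related-samples comparisons, by intention to treat and per protocol, and states: "Within-group effect sizes (pre vs post and pre vs 3-month follow-up) will be reported".

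Study Design describes a "within-group design with 3 measurement points at baseline (preintervention), immediately after the intervention (postbaseline), and 3-month follow-up". On timing, the intervention section says "It is estimated that the web-based intervention can be completed in 8 weeks", at the participant's own pace "with a maximum period of 10 weeks". Outcome Measures places the last wave at "3-month follow-up after they complete the intervention". Aims and Hypotheses adds: "We also hypothesize that gains will be maintained at 3-month follow-ups".

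**The concern.** A single random intercept with independent residuals is compound symmetry: one variance and one correlation for pre-post, post-follow-up and pre-follow-up alike. Every pairwise test then uses the same pooled error. In repeated questionnaire data the correlation usually falls as the gap grows, and here the longest gap (baseline to follow-up) is more than twice the shortest. A pooled error is then too small for the longest gap and too large for the pair with the highest correlation.

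At stake are the standard errors and p values of the change at 3 months, one of the two contrasts for which the article promises an effect size, and of the pre-to-post change. No planned analysis varies the covariance structure of the mixed model.

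**Working it through.** The article's only sample-size figure, a minimum of 35, is taken from a literature range and has no formula inputs. There is no power or precision figure to reproduce.

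**Inputs from the document**
- Three waves and n = 35 (Study Design, Sample Size).
- Pre to post 8 to 10 weeks; follow-up 3 months after completion, taken as 13 weeks. Baseline to follow-up is therefore 8 + 13 = 21 to 10 + 13 = 23 weeks.
- Bonferroni over three pairs.

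**Assumptions**
- Alpha is not stated in the article. Two-sided 0.05 is assumed, so 0.05/3 = 0.0167 per pair.
- Correlations are not given. Exponential decay in time is assumed, with r(pre, FU) from 0.4 to 0.7, and other patterns are tried alongside.
- Equal variances, complete data, no true change.

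**Formula.** With complete data and a positive intercept variance, the random-intercept REML fit equals repeated-measures ANOVA with pooled error on 2(n − 1) = 68 df:
- model SE² = 2σ²(1 − r̄)/n, where r̄ is the mean of the three correlations;
- true SE² for waves j and k = 2σ²(1 − r_jk)/n;
- ratio of model SE to true SE = √[(1 − r̄)/(1 − r_jk)].

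**Worked case**, post at week 8 and r(pre, FU) = 0.50:
- r(pre, post) = 0.50^(8/21) = 0.768; r(post, FU) = 0.50^(13/21) = 0.651; r̄ = (0.768 + 0.651 + 0.500)/3 = 0.640.
- Pre-FU: √(0.360/0.500) = 0.85, an SE 15% too small.
- Pre-post: √(0.360/0.232) = 1.25.
- Post-FU: √(0.360/0.349) = 1.02.

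**Simulation**, 40,000 trials per pattern, n = 35. Each cell gives the SE ratio, then the type I error at nominal 0.0167.

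| Correlations pre-post / post-FU / pre-FU | Pre-FU | Pre-post | Post-FU |
|---|---|---|---|
| Decay, week 8: 0.87/0.80/0.70 | 0.83; 0.047 | 1.28; 0.003 | 1.03; 0.014 |
| Decay, week 8: 0.77/0.65/0.50 | 0.85; 0.042 | 1.25; 0.003 | 1.02; 0.016 |
| Decay, week 10: 0.74/0.68/0.50 | 0.85; 0.039 | 1.18; 0.005 | 1.06; 0.011 |
| Decay, week 10: 0.67/0.60/0.40 | 0.86; 0.038 | 1.16; 0.006 | 1.05; 0.012 |
| Equal adjacent: 0.70/0.70/0.50 | 0.86; 0.041 | 1.11; 0.009 | 1.11; 0.009 |
| Equal adjacent, milder: 0.70/0.70/0.60 | 0.91; 0.028 | 1.05; 0.012 | 1.05; 0.012 |
| Pre-post lowered: 0.60/0.75/0.50 | 0.88; 0.036 | 0.98; 0.020 | 1.24; 0.004 |
| Pre-post below post-FU: 0.70/0.80/0.50 | 0.82; 0.051 | 1.05; 0.012 | 1.29; 0.002 |
| All equal: 0.60/0.60/0.60 | 1.00; 0.017 | 1.00; 0.017 | 1.00; 0.017 |

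Contrast-specific (paired) errors gave 0.015 to 0.018 for every pair in every pattern. With complete data these are also the standard errors of an unstructured covariance. Requiring a significant overall time effect first barely helps: for 0.70/0.80/0.50 it lowers the pre-FU rate only from 0.051 to 0.050.

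**The case against.** **The correlations are assumed.** This stands. With equal correlations the model is correct, and the size of the error depends on the decay.

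**The related-samples comparisons do not need equal correlations.** Read as paired tests, they are unaffected, and this mitigates the problem. It does not remove it: the mixed model is the analysis named for primary and secondary outcomes, and paired tests on observed data lose participants who miss a wave.

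**A final SAP is to come, and covariance details often sit there.** True, but the article does not leave the random part open. It fixes one random intercept per subject.

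**Feasibility is the main aim.** This stands and limits the severity.

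A reader might go further and infer that the model also blunts the post-to-follow-up test, so that both errors push towards a finding that gains are maintained. The documents do not support this:
- The second gap (about 13 weeks) is longer than the first (8 to 10). Under pure time decay the post-to-follow-up correlation lies near the average, so that test hardly changes. It is clearly blunted only if the intervention itself lowers the pre-post correlation.
- The contrast penalised most under pure decay is pre-to-post, which works against showing a gain. In the 0.77/0.65/0.50 case, power for a 0.3 SD shift is 0.335 with the pooled error and 0.541 with paired errors.
- The article never says that maintenance will be judged by a non-significant post-to-follow-up test.
- Power for a 0.25 SD loss is indeed low. With n = 30 and r = 0.7, SE = √(2 × 0.3/30) = 0.141, and power after Bonferroni is about 27%. That figure uses the correct standard error, so it reflects small n and Bonferroni, not the random intercept.

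**Conclusion.** The point holds for the baseline-to-follow-up contrast. The stated model assumes equal variances and equal correlations across unequally spaced waves, and no planned sensitivity analysis relaxes this. Under exponential decay on the article's own timing, with r(pre, FU) of 0.4 to 0.7, the baseline-to-follow-up standard error is 14 to 17% too small and type I error is 0.038 to 0.047 against 0.0167. Over all the unequal patterns tried, the ranges are 9 to 18% and 0.028 to 0.051. Pre-to-post is conservative under pure decay (0.003 to 0.006), and post-to-follow-up is little affected (0.011 to 0.016). These figures assume two-sided 0.05, complete data and equal variances.

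A systematic bias towards maintained gains is not shown. Severity is minor to moderate: the efficacy results are a preliminary, additional aim of an uncontrolled feasibility study, but a better specification is available at almost no cost.

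**What to change.** In the final SAP, keep the MIXED procedure but enter time as a repeated factor with an unstructured covariance (3 variances + 3 covariances = 6 parameters), in place of the random intercept. Use REML and Satterthwaite degrees of freedom. State in advance that a simpler heterogeneous structure is used only if the model does not converge.

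Also report the post-to-follow-up change with its 95% CI, so that maintenance is not inferred from a non-significant test. No particular non-loss margin follows from the documents.

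**Cost.** One line of syntax and one or two sentences, which the planned SAP revision before database lock can absorb. Six covariance parameters replace two at n of about 35. Where correlation decays, the baseline-to-follow-up interval becomes wider. In the worked case its 95% half-width goes from 1.995 × 0.1435 = 0.29 SD to 2.032 × 0.1690 = 0.34 SD. That is the correct width, not lost precision. The pre-to-post interval becomes narrower.

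### The listed missing-data sensitivity analyses all rest, as usually implemented, on missing at random, so their agreement would not show robustness to dropout that depends on unobserved lack of benefit

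*Protocol article*

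**What the plan says.** All references are to the Protocol article.

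- **Sensitivity analyses (Statistical Analysis Plan).** Their purpose is stated: "Sensitivity analyses will be performed to assess the robustness of the findings in terms of different methods for handling missing data". The methods follow in brackets after 'ie', so they read as the complete set: "mixed models with and without imputation, maximum-likelihood estimation, and maximum-likelihood multiple imputation".
- **Diagnostic (same section).** "The Little missing completely at random (MCAR) test will be used to assess the assumption that data are MCAR". Percentages and patterns of missing data will also be reported.
- **Efficacy analyses (same section).** There are related-samples comparisons on intention-to-treat and per-protocol sets, and a "linear mixed-effects models (MIXED) procedure with 1 random intercept per subject" for primary and secondary outcomes. The abstract names only mixed models for those outcomes.
- **Measurement times (Outcome Measures, Table 2).** PHI, the primary outcome, is collected at baseline, postintervention and 3-month follow-up only. The short affect scale (I-PANAS) is collected more often: "Pre, between modules, post, and FW".
- **Withdrawals (Recruitment).** The team will try to reach people who withdraw, to learn their reasons and gather feasibility data. Collecting outcome scores from them is not mentioned.
- **Use of the estimates (Sample Size).** At least 35 participants are planned, and the effect size and confidence interval are intended for powering a later randomised trial.

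**The concern.** A sensitivity analysis informs about an assumption only if at least one method in the set relaxes it. Likelihood-based mixed models and standard multiple imputation share one assumption: given the observed data, people with missing scores would have changed as those with scores did. Running several of them varies the computation and leaves that assumption in place.

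The design makes this more than a technicality. The programme is self-applied, without systematic telephone support, and there is no control arm. Someone who stops in an early module and completes no later assessment supplies one PHI value, the baseline. For that person, every MAR method in effect borrows the change seen in others with a similar baseline. If the person left because nothing was improving, the borrowed change is too large, and nothing in the PHI data can show it. Little's test does not help here, because it cannot separate MAR from missingness that depends on the unseen score.

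Two things are at stake: the preliminary efficacy estimate, and the effect size carried into the planning of the larger trial.

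**Working it through.** The plan has no figure of its own to reproduce. The 35 is chosen from a recommended range of 24 to 50, and no dropout allowance is stated. Two checks were made.

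**1. Arithmetic**

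Inputs:
- Completer gain of 0.50 SD: assumed, as a moderate effect consistent with the article's hypothesis.
- Gain in those with missing scores of 0: assumed.
- Proportion missing *p*: 11.6% is the dropout rate of a web-based trial cited in the Introduction; 30% is assumed. The article gives no planning value for this study.

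Formula: overall change = 0.50 × (1 − *p*) + 0 × *p*.

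| *p* | Overall change | Overstatement if 0.50 is reported | Ratio of required n, (0.50 / overall)² |
|---|---|---|---|
| 11.6% | 0.50 × 0.884 = 0.442 | 0.50 / 0.442 = 1.13 | 1.28 |
| 30% | 0.50 × 0.70 = 0.35 | 0.50 / 0.35 = 1.43 | 2.04 |

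The last column uses the fact that required sample size scales with 1/d².

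For scale, with about 31 complete pairs (35 × 0.884 = 30.9) and d = 0.5, the 95% CI half-width is about 1.96 × √(1/31 + 0.5²/(2 × 31)) = 0.37. The gap at 11.6% is 0.50 − 0.442 = 0.058.

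**2. Illustrative simulation**

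All settings are assumptions: baseline SD 1, true mean change about 0.50, pre-post correlation 0.6, and logistic dropout that removes both the post and follow-up scores. Samples were made large (20,000; 3,000 for the mixed model) so that differences show bias and not chance.

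| Dropout driven by | Missing | Truth | Complete pairs | ML/MI under MAR | Random-intercept model | Return to baseline |
|---|---|---|---|---|---|---|
| Poor change (not MAR) | 16% | 0.50 | 0.63 | 0.60 | 0.63 | 0.53 |
| Poor change (not MAR) | 33% | 0.50 | 0.74 | 0.70 | 0.67 | 0.50 |
| Baseline only (MAR) | 15% | 0.50 | 0.45 | 0.50 | 0.51 | 0.38 |
| Baseline only (MAR) | 33% | 0.49 | 0.38 | 0.49 | 0.49 | 0.26 |

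When dropout follows poor change, the MAR methods lie close together and all lie above the truth. When dropout depends only on baseline, the MAR methods recover the truth and complete pairs do not. The listed methods therefore protect against the second kind of dropout and give no warning of the first.

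The last column shows that returning people to baseline is a scenario and not a correction. It is close to the truth in the first two rows and well below it in the last two. It belongs beside the main estimate, not in place of it.

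**The case against.** The strongest case against has four parts.

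**The text does not fix MAR.** The imputation paired with the mixed models is not specified. Carrying the baseline forward would itself give leavers zero gain. This stands, and it is why the point is limited to ordinary implementation. But nothing in the list says that a departure from MAR is intended.

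**Details belong to the final SAP, and efficacy is preliminary.** Both are true and limit the weight of the point. However, the article goes beyond leaving the matter open: it states a purpose and a closed set of methods that, as usually run, does not serve it.

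**The size is assumed.** It follows entirely from zero gain in those with missing scores. Table 2 defines attrition as leaving the intervention, which need not mean a missing PHI score. At 11.6% the gap of 0.058 is about one sixth of the CI half-width of 0.37. All of this stands.

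**Some information on leavers exists.** Missing-data patterns and reasons for withdrawal will be reported. These are useful descriptions, but they do not show how far the estimate would move.

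A reader might also infer stronger criticisms that the article does not support:

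- *That the intention-to-treat comparison discards anyone without a second score.* The wording is "means of comparison for related samples based on intention-to-treat and per-protocol analyses". A paired test does this by default without imputation, but the article does not say how an incomplete pair is handled, and it mentions imputation.
- *That no analysis is given the lead.* The abstract assigns primary and secondary outcomes to mixed models.
- *That I-PANAS goes unanalysed.* It is a listed secondary outcome. Only its between-module scores have no stated role in the Statistical Analysis Plan.
- *That the planned methods can never pick up dropout linked to lack of benefit.* Where poor response shows in observed data, such as a low post score before a missed follow-up, MAR methods adjust for part of it.

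**Conclusion.** The point holds in this limited form. As ordinarily implemented, the listed sensitivity analyses share the MAR assumption, and Little's test cannot check it against dropout that depends on unseen scores. Agreement among them would therefore not be evidence of robustness to that kind of dropout. The criticism applies most fully to PHI in people who leave during the modules with only a baseline value.

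The size is illustrative: 0.44 or 0.35 in place of 0.50 at 11.6% or 30% missing, conditional on zero gain in those with missing scores and on dropout meaning a missing score. The documents do not show that the estimate will be biased, or by how much. They show that the planned set could not reveal such a bias. At a low rate of missing scores the effect is small against sampling error. At an assumed 30%, a later trial planned on 0.50 would need about twice the sample size if the overall change were 0.35. The change is worth making but is not critical to the feasibility aims.

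**What to change.** In the final SAP, before database lock:

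1. Keep the mixed model on all allocated participants as the main analysis, as the abstract indicates.
2. Add one delta-adjusted multiple imputation for PHI. Impute under MAR, lower the imputed scores by a stated range of deltas, and report the pre-post effect with its 95% CI at each value. Include a scenario in which participants with missing scores return to their own baseline.
3. Use baseline PHI, last module reached and the between-module I-PANAS scores as auxiliary variables in the imputation. Baseline PHI and I-PANAS are already collected, and the last module reached should be derivable from the platform's usage records.
4. Report Little's test as descriptive only, and do not let its result choose or justify the method.

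No new data collection is needed. The cost is SAP wording, a little more programming, and one more conservative estimate shown beside the main one.
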